# Effects on nurses’ quality of working life and on patients’ quality of life of an educational intervention to strengthen humanistic practice among hemodialysis nurses in Switzerland: a protocol for a mixed-methods cluster randomized controlled trial

**DOI:** 10.1186/s12912-018-0320-0

**Published:** 2018-11-21

**Keywords:** Educational intervention, Humanistic nursing practice, Watson’s theory of human caring, Mixed method design, Quality of working life of haemodialysis nurses, Quality of life of haemodialysis patients, Team cohesion

## Abstract

**Background:**

Humanistic nursing practice constitutes the cornerstone of the nursing profession. However, according to some authors, such practice tends to fade over time in favour of non-humanistic behaviours. To contrast this tendency, an educational intervention (EI) based on Watson’s Theory of Human Caring was developed and tested in two pilot studies involving, respectively, rehabilitation nurses in Quebec (Canada) and haemodialysis (HD) nurses in Switzerland. In light of the positive results obtained in these, another study is being undertaken to examine more in depth the EI’s effects on both HD nurses and patients in French Switzerland. The EI is expected to have positive effects on quality of nurse-patient relationship (NPR), team cohesion, nurse quality of working life (QoWL), and patient quality of life (QoL).

**Methods/design:**

The study described in this protocol will use a mixed-method cluster randomised controlled trial design. For the quantitative component, nurse and patient data will be collected through questionnaires. The accessible population of 135 nurses and 430 patients will be clustered into 10 HD units. These units will be randomised into an experimental group (EG) and a waiting-list control group (WLCG). Measurements will be taken at baseline (pre-intervention) and repeatedly over time (post-intervention): immediately at EI completion and six and 12 months thereafter. For the qualitative portion of the study, 18 semi-structured interviews will be conducted with EG nurses picked at random two months after EI completion to explore perceived changes in nurse humanistic practice. Qualitative data will be analysed through the relational caring inquiry method, a phenomenological approach. Descriptive and inferential statistics will be computed from the quantitative data.

**Discussion:**

The study described in this protocol will determine if and how the proposed EI promotes humanistic nursing practice and how this practice affects quality of NPR, nurse QoWL, and patient QoL. Moreover, it will lay the groundwork for offering the EI to nurses in other healthcare sectors.

**Trial registration:**

This clinical study was registered with ClinicalTrials.gov [NCT03283891, 14/09/2017].

## Background

Humanistic nursing practice, including caring, has been a matter of interest to nursing researchers for several decades now. Their studies of the subject have tended to underscore what distinguishes nursing from the other health professions. In this regard, Watson [1] stated that the Theory of Human Caring could serve to guide clinical nursing practice by enabling it to transcend the physical dimensions of the care recipient in order to grasp the whole of the care situation as experienced by the person. More specifically, Watson [1] defines nursing care as helping people give meaning to their existence, suffering, and disharmony by means of a caring relationship. The relationship that nurses cultivate with patients and their families corresponds to a human process that Watson [1] calls the “transpersonal caring relationship”. This is a genuine relationship that requires nurses to base their practice on a system of humanistic-altruistic values that allows patients and their families to grow in an environment conducive to the development of potential [1]. Caring rests on humanistic values that influence attitudes, which in turn guide behaviours. This results in a more humanistic professional practice [1]. According to Cara [2], the attitudes required for nurses to engage in such practice can be developed and strengthened. These include authentic presence, compassion, active listening, understanding, support, reciprocity, and collaboration.

Various authors have documented the therapeutic effects of the caring relationship both on nurses [3], in terms of improved sense of self-esteem, well-being, and personal achievement, and higher levels of work satisfaction [4, 5], and on patients, in terms of improved autonomy, independence, hope [6], and quality of life (QoL) [7], and greater satisfaction with nursing care received [8]. Empirical studies have also shown that the caring relationship contributes to develop a sense of security among patients [5] and to lower hospital readmission rates, in particular among patients with heart failure [9].

Other studies [10–16] have raised awareness of the presence of dehumanising nursing care practices in clinical settings, the effects of which can be devastating for nurses and patients alike. According to the results of a literary meta-analysis by Swanson [14], patients confronted with nurse uncaring attitudes and behaviours feel humiliated, frightened, powerless and vulnerable, and this can contribute to lengthen physical healing times. Moreover, uncaring practices [14] can, for the nurses themselves, lead to burnout and depression and generate the impression of working like an automaton. Though the majority of these studies have been carried out in the United States, similar results have been reported recently in European countries and Canada. In a phenomenological study involving 23 rehabilitation inpatients in Quebec aimed at exploring the meaning and contribution of “being with” a nurse, O’Reilly et al. [17] highlighted various dehumanising elements in nursing practice, including lack of listening, understanding and the objectification of patients. In France, a vast patient-initiated survey on the consequences of kidney disease was undertaken in 2012–2013 within the framework of the “États généraux du rein” [convention of kidney health stakeholders; http://www.renaloo.com/images/stories/EGR/rapport%20final.pdf], in which some 7000 patients undergoing haemodialysis (HD) completed a questionnaire. The results obtained indicated that uppermost among proposed areas of improvement was the quality of the nurse-patient relationship (NPR). The patients underscored that attending staff should demonstrate empathy and a willingness to listen to them and should take the time to explore their needs, which was not always the case.

Against this background and with a view to reviving nursing humanistic practices in care settings, an educational intervention (EI) was developed in Quebec [18, 19] on the basis of Watson’s Theory of Human Caring [20, 21]. The intervention was implemented and evaluated in two pilot studies, first, qualitatively in a population of rehabilitation nurses in Quebec [19] and, then, with mixed methods in a population of HD nurses in French Switzerland [22]. The choice of these two populations rested on the fact that nurse presence and quality of nurse-patient interactions play a key role in patient QoL [23, 24]. Both studies [19, 22] showed that the EI had a high acceptability and feasibility level. Furthermore, a secondary qualitative analysis of the two pilot studies [25] showed that results converged in large part regarding the intervention’s feasibility, acceptability and benefits for nursing practice. This convergence justifies the implementation now of a large-scale experimental study [26, 27] to test the effects of the EI on various outcome variables, including quality of working life (QoWL) of nurses, QoL of patients in their care, and quality of NPR.

### Theoretical framework

In order to enhance the validity of the research through the judicious choice of a theoretical framework [28] to orient the selection of the variables to explore, we propose grounding the study described in this protocol in Duffy and Hoskins’ Quality-Caring Model [9], a middle-range theory that serves to understand the NPR as theorised on the basis of Watson’s 10 carative factors (CF) [20, 21] and to interpret the emergence of positive outcomes for patients, families, health professionals and, more broadly, the healthcare system [29]. According to this model, the NPR is therapeutic for patients by helping raise their QoL and their satisfaction with care. Thus, quality of NPR is a major factor in patient health and an indicator of care quality and patient safety [9]. According to Donabedian’s quality paradigm [30], Duffy and Hoskins’ model [9, 29] can be broken down into three parts: structure, process and outcome. **Structure** includes all factors related to nurses, patients and the healthcare system upstream from care delivery. Where nurses are concerned, these encompass sociodemographic characteristics (e.g., age, years of experience, educational level, shift) and workload-related variables (e.g., patient-nurse ratio, overtime hours worked, team cohesion). For the purpose of our study, we will measure nurse-perceived quality of NPR and QoWL prior to the intervention. As for the patients, we will document sociodemographic characteristics, severity of illness, and comorbidity. We will also measure patient-perceived quality of NPR and QoL. These variables are compatible with the elements that compose Duffy and Hoskins’ model [9, 29]. The measures taken prior to the intervention (pre-test) will provide baseline values. **Process** [9, 29] refers to nurse clinical practice, especially in connection with the caring relationship that nurses cultivate with care recipients. The caring relationship is at the heart of the process and reflects nurse commitment to caring for patients. It is in this light that the relevance of delivering an EI based on the concepts of Watson’s theory [20, 31] becomes clear, given that the intervention is intended to mobilise and consolidate nurse abilities to dispense care according to the caring approach. This is all the more important in HD units where nursing practice revolves around tech-heavy tasks [24]. **Outcome**, the last component of the theory, comprises two levels: intermediate and terminal. For Duffy and Hoskins [9, 29], **intermediate outcomes** correspond to changes in attitudes/behaviours among carers, patients or an organisation, which lead to changes in the orientation of the clinical follow-up of patients. In our study, the following intermediate outcomes will be examined: 1) nurse-perceived changes in caring attitudes/behaviours and patient-perceived changes in nurse caring attitudes/behaviours post-intervention; 2) nurse-perceived changes in team cohesion post-intervention; and 3) quality of NPR. To this end, nurses and patients will complete measures of quality of NPR post-intervention. Moreover, phenomenological qualitative interviews will be conducted with nurses to obtain additional information on their perception of change in quality of NPR post-intervention. Finally, **terminal outcomes** are tied to the major concepts that can affect the future of both HD patients and nurses. In our study, patient QoL and nurse QoWL will be the primary outcomes of the study. In sum, the Quality-Caring Model [9, 29] will provide a solid theoretical structure for examining the effects of the intervention on both the nurses and the patients participating in the research.

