#### Primary objectives

1) Describe levels of the variables of interest among nurses (quality of NPR, team cohesion, QoWL) and patients (quality of NPR, QoL) pre-intervention (T0); and 2) examine the effects of the intervention on the variables of interest among participating nurses and patients immediately post-intervention (T1) and twice more over time (T3 and T4).

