#### Proposed hypotheses

Based on Duffy and Hoskins’ framework [9, 29] and in accordance with the main objectives of this research, we will make the following statistical hypotheses: 1) post-intervention, frequency of nurse caring attitudes/behaviours will be higher in the experimental group (EG) vs a waiting-list control group (WLCG); 2) post-intervention, team cohesion level will be higher in the EG vs the WLCG; 3) post-intervention, level of nurse QoWL will be higher in the EG vs the WLCG; 4) post-intervention, patient-perceived frequency of nurse caring attitudes/behaviours will be higher in the EG vs the WLCG; and 5) post-intervention, level of patient QoL will be higher in the EG vs the WLCG.

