### Data analysis

For the quantitative component of the study described in this protocol, first, we will check the data for inclusion conditions and outliers. Outlying data will be verified individually. Second, associations between factors and outcomes will be described using frequencies, means and standard deviations or medians and interquartile ranges. In addition, these associations will be evaluated using chi-square tests, Fisher tests or analyses of variance. Third, linear regression models adjusted for significant sociodemographic and health variables will be used to examine the intervention’s effect on the different variables selected for the study, keeping in mind that nurse QoWL remains the key outcome variable. Moreover, we will consider a random intercept to take HD unit variance into account. Fourth, we will test whether team cohesion acts as a mediator in the relationship between NPR (independent variable) and nurse QoWL (outcome variable). For this purpose, we will run three regressions: 1) regression of mediator on independent variable (EIIP-70); 2) regression of outcome variable (QoWL) on independent variable; and 3) regression of outcome variable on both independent variable and mediator. Fifth, an intention-to-treat analysis will be conducted of the data on all participants, whether they complete the intervention or not. This will diminish bias related to protocol deviations or withdrawals and will allow estimating the intervention’s effects under conditions that are close to real life. Sixth, based on sample size and sample design (10 HD units of different sizes for a total of 135 nurses) and considering an intra-class correlation coefficient of 0.03 for the HD units, we will be able to detect an effect size of 0.6, with statistical power of 0.8 and significance level at 0.05 for all analyses. The expected effect size has been fixed by the investigators and corresponds to the minimal clinically significant effect. The intra-class correlation coefficient selected is in line with Giraudeau’s recommendations [52] of 0.001 to 0.05 for a cluster RCT. The data will be analysed using the R software [54].

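### The protocol is inconsistent about what is primary (two outcomes, one key outcome, or five variables at three times) and gives no primary time point or testing order, with 0.05 set for all analyses

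*Protocol article*

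**What the plan says.** Four places in the protocol article bear on what is primary.

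- **Theoretical framework:** two primary outcomes. "In our study, patient QoL and nurse QoWL will be the primary outcomes of the study". Caring attitudes and behaviours, team cohesion and quality of NPR are put in a different class: "In our study, the following intermediate outcomes will be examined".
- **Primary objectives:** five variables, namely the "variables of interest among nurses (quality of NPR, team cohesion, QoWL) and patients (quality of NPR, QoL"). The second objective is to estimate effects on them "immediately post-intervention (T1) and twice more over time (T3 and T4").
- **Proposed hypotheses:** five directional hypotheses, one per variable, introduced with "in accordance with the main objectives of this research, we will make the following statistical hypotheses". Each is dated only as post-intervention.
- **Data analysis:** a single lead outcome, "keeping in mind that nurse QoWL remains the key outcome variable". The power sentence in the same section rests on the 135 nurses and gives a "significance level at 0.05 for all analyses".

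Table 2 shows three quantitative post-intervention measurements (T1, T3, T4). No section picks one of them as primary, ranks the outcomes for testing, or says what result would count as success.

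**The concern.** The primary outcome settles which result answers the trial's question. Here a reader can find support for one, two or five candidates, each measured three times after the intervention. An analysis plan, if one exists, cannot carry out all of these statements; it would have to override at least one of them.

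Two things are at stake. First, the false-positive rate over whatever is treated as primary exceeds 5% when each test is run at 0.05. Second, the choice of outcome and time could be made, or appear to have been made, after results are known. The second risk is practical: the Study design section says that the researchers are not blinded (data entry and analysis go to a separate group), and the Preliminary results section reports that the first data wave is complete and the intervention has been delivered to the experimental group.

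**Working it through.** **1. What each section makes primary**

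| Section | Primary or lead variables | Times |
|---|---|---|
| Theoretical framework | 2: nurse QoWL, patient QoL | not given |
| Primary objectives | 5: nurse NPR, team cohesion, QoWL; patient NPR, QoL | T1, T3, T4 |
| Proposed hypotheses | 5, one per variable | post-intervention only |
| Data analysis | 1 key outcome: nurse QoWL | not given |

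**2. The plan's own power figure**

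Inputs from Data analysis: 135 nurses, 10 units, ICC 0.03, effect size 0.6, level 0.05 (two-sided assumed), power 0.8. From Sampling procedure: at least 50 nurses per arm, so the split lies between 67.5/67.5 and 50/85. The coefficient of variation (CV) of unit size is not given; 0 to 0.5 is assumed.

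- Design effect = 1 + [(1 + CV²) × 13.5 − 1] × 0.03. This is 1.375 at CV 0 and 1.476 at CV 0.5.
- SE = √[DE × (1/n₁ + 1/n₂)]; power = Φ(0.6/SE − 1.96).
- CV 0, equal split: SE = √(1.375 × 2/67.5) = 0.202; 0.6/0.202 = 2.97; power 0.844.
- CV 0.5, 50/85 split: SE = 0.217; 0.6/0.217 = 2.77; power 0.791.

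The stated 0.8 therefore reproduces by normal approximation for **one** nurse comparison at 0.05. (A t test on 8 degrees of freedom would give about 0.68–0.74 over the same cases; that is a separate matter.) No power figure is given for patient QoL.

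**3. Chance of at least one p<0.05 under no effect**

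For k independent two-sided tests: 1 − 0.95^k.

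- k = 3 (nurse QoWL at three times): 1 − 0.95³ = 14.3%
- k = 6 (two outcomes × three times): 1 − 0.95⁶ = 26.5%
- k = 15 (five variables × three times): 1 − 0.95¹⁵ = 53.7%

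The tests would be correlated. The documents give no correlations, so these are assumed: 0.6–0.8 between times and 0–0.5 between outcomes. Multivariate-normal simulation, 400,000 draws per setting:

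| Tests | Either direction | Favourable direction only |
|---|---|---|
| 3 | 10–12% | 5–6% |
| 6 | 17–22% | 9–12% |
| 15 | 33–47% (33–44% if outcomes correlate at 0.3 or more) | 17–26% |

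Nurse QoWL and patient QoL come from different people, linked only through the unit. A between-outcome correlation near zero is therefore plausible for the six-test case; with zero it gives 19–22%.

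**4. What correction by splitting alpha would cost**

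Bonferroni power for a nurse comparison (CV 0–0.5, both splits): over 2 tests (0.025 each) 0.70–0.77; over 6 (0.0083) 0.55–0.63; over 15 (0.0033) 0.43–0.52. A fixed testing order with one contrast per outcome leaves the first test at 0.05 and keeps the planned power.

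**The case against.** The passages can be partly reconciled. Only the Theoretical framework section uses the term primary outcomes, and it names two. The Primary objectives section lists objectives, the first of which is purely descriptive. Calling nurse QoWL key could mean that it leads two primaries. The 0.05 level appears in the power sentence and is at least partly a design assumption. Multiplicity handling is often left to an analysis plan, which is not shown, and this is a condensed article.

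Much of this is fair, and it limits the claim. A reader might infer that fifteen primary tests are planned. The documents do not say so: they do not state whether T1, T3 and T4 are tested separately or in one model, so fifteen is only an upper bound. A reader might also infer that any single significant result would be called success. No section says that either; what is missing is a rule that excludes it. The favourable-direction figures are closer to the risk of a false claim of benefit, because all five hypotheses are directional.

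The conflict itself remains. The text does not state the reconciled reading, and the Proposed hypotheses tie all five variables to the main objectives. Even nurse QoWL alone leaves three time points with none chosen. The level is expressly given for all analyses, so the issue is a conflict in stated text and not just detail deferred to another document.

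**Conclusion.** The concern holds as an inconsistency about what is primary, together with no primary time point and no order of testing at a common 0.05 level. On the two named primary outcomes at three times, the chance of at least one false-positive result is 26% if independent and about 17–22% under the assumed correlations, or about 9–12% in the favourable direction. On nurse QoWL alone it is about 10–14%. The upper bound of fifteen tests gives 54% if independent and roughly a third to under a half if correlated.

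These figures assume separate two-sided tests at each time, and the correlations are not from the documents. If the time points are in fact tested jointly, or one is chosen in advance, the figures fall: two outcomes on one contrast each give at most about 10% (1 − 0.95² = 9.75% if independent), and nurse QoWL alone on one contrast gives 5%. The nurse power figure is not undermined; it stands for one comparison at 0.05, which is what a single named primary contrast would use.

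**What to change.** Make the Theoretical framework, Primary objectives and Data analysis sections agree, following the priority the protocol already implies.

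1. **First primary outcome:** nurse QoWL, total score, with one pre-specified between-arm contrast tested at 0.05. The contrast is either one named time point or the average over T1, T3 and T4. The hypothesis wording allows either, so the choice must be stated. Averaging needs a participant-level random effect in addition to the HD-unit intercept now described.
2. **Second primary outcome:** patient QoL, one named WHOQOL-BREF score, on the same contrast, tested at 0.05 only if the first test is significant.
3. **All else:** NPR, team cohesion and the other time-specific contrasts are labelled secondary or exploratory.
4. **Timing:** settle this before any post-intervention comparison by arm, from T1 onward, is examined. If some have been examined already, report that.

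The change needs no new data; if the averaged contrast is chosen, the model statement changes as well. The downside is that some results can no longer be presented as confirmatory, and patient QoL is confirmatory only if nurse QoWL succeeds.

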
### Aim of research and objectives

The aim of the study described in this protocol is to evaluate the effects on quality of NPR, team cohesion, nurse QoWL, and patient QoL of an EI intended to reinforce the humanistic practices of nurses in French-Swiss HD units.

#### Primary objectives

1) Describe levels of the variables of interest among nurses (quality of NPR, team cohesion, QoWL) and patients (quality of NPR, QoL) pre-intervention (T0); and 2) examine the effects of the intervention on the variables of interest among participating nurses and patients immediately post-intervention (T1) and twice more over time (T3 and T4).

